## Abstract

**Background and objective:**

Cerebral microembolism detected by transcranial Doppler (TCD) occurs systematically during cardiac catheterization, but its clinical relevance, remains unknown. Studies suggest that asymptomatic embolic cerebral infarction detectable by diffusion-weighted (DW) MRI might exist after percutaneous cardiac interventions with a frequency as high as 15 to 22% of cases. We have set up, for the first time, a prospective multicenter trial to assess the rate of silent cerebral infarction after cardiac catheterization and to compare the impact of the arterial access site, comparing radial and femoral access, on this phenomenon.

**Study design:**

This prospective study will be performed in patients with severe aortic valve stenosis. To assess the occurrence of cerebral infarction, all patients will undergo cerebral DW-MRI and neurological assessment within 24 hours before, and 48 hours after cardiac catheterization and retrograde catheterization of the aortic valve. Randomization for the access site will be performed before coronary angiography. A subgroup will be monitored by transcranial power M-mode Doppler during cardiac catheterization to observe cerebral blood flow and track emboli. Neuropsychological tests will also be recorded in a subgroup of patients before and after the interventional procedures to assess the impact of silent brain injury on potential cognitive decline. The primary end-point of the study is a direct comparison of ischemic cerebral lesions as detected by serial cerebral DW-MRI between patients explored by radial access and patients explored by femoral access. Secondary end-points include comparison of neuropsychological test performance and number of microembolism signals observed in the two groups.

**Implications:**

Using serial DW-MRI, silent cerebral infarction rate will be defined and the potential influence of vascular access site will be evaluated. Silent cerebral infarction might be a major concern during cardiac catheterization and its potential relationship to cognitive decline needs to be assessed.

**Study registration:**

The SCIPION study is registered through National Institutes of Health-sponsored clinical trials registry and has been assigned the Identifier: NCT 00329979.

## Background

Acute cerebral infarction following cardiac catheterization is rare [1-3], but silent brain injury could occur at an unexpectedly high rate [3-6] as detected by diffusion-weighted (DW) magnetic resonance imaging (MRI). Indeed the high sensitivity of DW-MRI suggests that this technique could allow an improved estimate of cerebral ischemic events associated with cardiovascular catheterization procedures and could be used therefore as a surrogate endpoint for risk assessment of stroke [7]. The use of transcranial Doppler (TCD) sonography allows the recording of microemboli entering the middle cerebral artery during various endovascular interventions, including cardiac catheterization [8,9]. In the case of coronary bypass surgery, evidence indicates that microembolism might be related to cognitive impairment, based on the results of neuropsychological testing [10]. During cardiac catheterization, cerebral microembolism as detected by TCD has frequently been observed, but whether it is clinically relevant remains unknown [8,9]. However, recent studies mentioned above, have suggested that some of these microemboli could be related to silent cerebral embolisms responsible for acute ischemic brain injury, as documented by DW-MRI [3-6]. Furthermore there is increasing evidence that cumulative burden of ischemic brain injury causes neuropsychological deficits or aggravates vascular dementia [11]. Thus DW-MRI emerges as a valuable diagnostic method for the monitoring of periprocedural ischemic events in the brain and could be considered as a surrogate parameter for optimising diagnostic and therapeutic vascular interventions.

In the present trial two vascular access sites (trans-radial approach [TRA] and trans-femoral approach [TFA]) routinely used for cardiac catheterization and percutaneous cardiovascular interevention (PCI) will be compared for the risk of silent brain injury occurrence. Indeed TRA is associated with fewer local complications and it has been suggested that in particular right TRA, which avoids crossing the aortic arch could reduce the risk of mobilization of atherosclerotic plaque, present particularly within the aortic arch as documented previously by several authors [12-14]. However this risk of brain injury in relation to vascular access site remains largely debatable. Using DW-MRI as a surrogate parameter for brain injury assessment we propose a prospective evaluation of the occurrence of silent brain lesions in patients randomized either to TRA or TFA.

## Design and methods

### Study design

Prospective multicenter randomized trial (4 centers currently involved: 2 in France, 1 in Italy and 1 in Austria).

### Study objectives

1. Assessment in a prospective multicenter trial of the rate of silent brain injury after cardiac catheterization

2. Comparison of the TRA and the TFA on the occurrence of new cerebral lesions as detected by DW-MRI

3. Implication of silent brain infarction(s) on potential cognitive impairment

### End points

#### (i) Primary end-point

Number of patients observed with new cerebral lesions either symptomatic or not after cardiac catheterization as detected by DW-MRI in each group (comparison of radial and femoral access).

#### (ii) Secondary end-points

Impact of potential silent cerebral infarction on cognitive impairement.

Number of microembolism signals observed at TCD between the two groups.

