### Neuropsychological assessment

Patients will undergo neuropsychological assessment within 24 hours before, and 48 hours after, cardiac catheterization. All patients with documented cerebral infarction at DW-MRI will be asked to come back for a new neuropsychological assessment at 1 year follow-up.

The aim of the cognitive testing is to provide clinical evidence of potential cerebral damage after cardiac catheterization and to quantify this potential cognitive decline allowing comparison of two groups of patients explored either by radial or femoral approaches. The tests must be sensitive enough to detect potential post-procedure cognitive decline and also able to explore different brain areas. Most of the neuropsychological tests that will be administered have been reported to be sensitive to change after CABG or PCI procedures [19] and will include: Digit Span Forwards and Backwards, Trail making test A and B, Wechsler Memory Scale visual reproduction test, Rey-Osterrieth's figure test, Grober-Buschckle's test, Rey Auditory Verbal Learning Test, Verbal fluency test, and Confrontation naming test.

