### Statistical analysis

Baseline characteristics of the study population will be presented as counts and percents for categorical variables and as mean ± SD for continuous variables. Kappa statistic will be calculated to determine interobserver agreement. The number of lesions in our population of patients recruited will be estimated by the adjusted Wald interval at 95% in accordance with the method recommended by Agresti & Coull [20]. With small sample sizes, as recommended we will use the mid-point of the adjusted Wald interval instead of the observed proportion [21]. The statistical analyses will be performed using SPSS 10.0.7 software (Chicago, IL, USA). The compound score for global cognitive function will be constructed by calculating the average of the z scores for all the above tests. Cognitive decline will be calculated by subtracting the z scores for memory performance, psychomotor speed, and global cognitive function at follow-up from the z scores at base line. All analyses will be adjusted for age, sex, and level of education, as well as the interval between the two sets of neuropsychological tests.

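### The cognitive secondary endpoint is stated both as a comparison of access arms and as an effect of infarction, and the single covariate set leaves the infarction version open to confounding by arm

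*Protocol article*

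**What the plan says.** The protocol article states the cognitive question in five places.

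- **Abstract, Study design.** The tests are done "to assess the impact of silent brain injury on potential cognitive decline". Two sentences later the endpoint becomes an arm comparison: "Secondary end-points include comparison of neuropsychological test performance and number of microembolism signals observed in the two groups".
- **Study objectives, item 3.** "Implication of silent brain infarction(s) on potential cognitive impairment". No arm comparison is named.
- **End points, (ii) Secondary end-points.** "Impact of potential silent cerebral infarction on cognitive impairement". Again no arm comparison is named, although the next line of the list, on microembolism signals, does compare the two groups.
- **Neuropsychological assessment.** The testing is meant "to quantify this potential cognitive decline allowing comparison of two groups of patients explored either by radial or femoral approaches".
- **Statistical analysis.** Cognitive decline is a change in z scores between baseline and follow-up, and "All analyses will be adjusted for age, sex, and level of education, as well as the interval between the two sets of neuropsychological tests". The text does not say whether this serves the arm contrast, the infarction contrast or both.

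**The concern.** The two statements are different questions. Comparing radial with femoral patients is protected by randomisation. Comparing patients with and without a new lesion conditions on something that happens after randomisation, so it is observational even though it sits inside a randomised trial.

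Two things are at stake. First, the contrasts can give different answers on the same data, and the document allows either to be reported as the planned cognitive endpoint. Second, the stated covariates do not include access arm. The trial's own hypothesis is that arm strongly determines who gets a lesion. If access also affects early test performance by some other route, part of that effect would be credited to the infarct.

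**Working it through.** **Inputs.** From Sample size calculation: new-lesion rates of 5.9% radial (95% CI 0.01 to 12.5) and 23% femoral (15 to 31), 76 patients per arm, alpha 5%, power 80%. I assume that all 152 patients are tested. This is a best case, since the abstract says that only a subgroup is, without giving its size. Effects on cognition are in SD units and are assumptions, because the document gives none.

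**Reproducing the plan's figure.** The two-sided comparison of two proportions with pooled variance needs 66 per arm. With continuity correction it needs 77 per arm (154 in total), close to the stated 76 (152). The rates below are therefore the ones behind the design.

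**Expected lesions.**
- Radial: 76 × 0.059 = 4.5. Femoral: 76 × 0.23 = 17.5. Total about 22.
- Without a lesion: 71.5 radial + 58.5 femoral = 130.

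**How different the two contrasts are.** Minimum detectable difference = (1.96 + 0.84) × √(1/n₁ + 1/n₂).
- By arm, 76 v 76: 2.80 × √(2/76) = 0.45 SD.
- By lesion, 22 v 130: 2.80 × √(1/22 + 1/130) = 0.65 SD.

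Suppose an infarct costs 0.5 SD and access acts only through infarcts.
- The arm difference is (0.23 − 0.059) × 0.5 = 0.171 × 0.5 = 0.086 SD. Power with 76 per arm is about 8%, and 80% power would need about 2,148 per arm.
- The lesion contrast has standard error √(1/22 + 1/130) = 0.23, so 0.5/0.23 = 2.17 and power is Φ(2.17 − 1.96), about 58%.

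The same truth could easily give a null result on one contrast and a positive result on the other.

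**Arm imbalance in the lesion contrast.**
- Femoral share of lesion-positive patients: 17.48/21.96 = 79.6%.
- Femoral share of lesion-negative patients: 58.52/130.04 = 45.0%.
- Difference: 0.346.

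In an additive model without arm, a direct arm effect D adds D × (difference in femoral share) to the apparent lesion effect. Age, sex and education are balanced between arms by randomisation in expectation, so adjusting for them does not remove this term.

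| Radial rate | Femoral rate | Bias |
|---|---|---|
| 5.9% | 23% | 0.35D |
| 12.5% | 15% | 0.05D |
| 12.5% | 31% | 0.27D |
| 0.01% | 15% | 0.54D |
| 0.01% | 31% | 0.59D |

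At the planned rates, D = 0.1, 0.2 or 0.3 SD gives a bias of 0.03, 0.07 or 0.10 SD. If access affects cognition only through DW-MRI lesions, D is zero and so is the bias.

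**The case against.** The strongest reply is that the document pursues two compatible questions and lists them unevenly. The abstract contains both, so it is not a case of the abstract saying one thing and the endpoint list another. That is right, and it limits the criticism to the lack of a clear statement. It does not remove it: the formal list and the objectives name one contrast, while the abstract's endpoint sentence names the other.

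A second reply is that a condensed article may leave a full model to the analysis plan. That stands for detail that is simply absent. But here the article does state a covariate set and applies it to all analyses, so it is fair to point out that the set does not suit both contrasts. For the arm contrast nothing is missing, since arm is then the exposure.

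Third, a reader might infer that the lesion contrast is confounded by arm. The document does not support that. It needs a route from access to cognition other than DW-MRI lesions. The Background raises microembolism as a possible cause of cognitive impairment, but for bypass surgery. Pain or immobilisation after one access route is not mentioned anywhere. The contrast is open to this confounding, not shown to suffer from it.

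Fourth, a reader might infer that poorer cognition at baseline would be mistaken for harm from the new lesion. The outcome is a change score, so a stable deficit cancels, and baseline score is already partly handled. What remains is the possibility that patients with older lesions change differently. The primary endpoint counts only new lesions, but that separates old lesions from the exposure without adjusting for them.

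**Conclusion.** The cognitive secondary endpoint has two definitions, and the passages need to be reconciled. This holds whatever is assumed about bias: one contrast is randomised at 76 v 76, the other observational at about 22 v 130, and the figures would be smaller in a tested subgroup.

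The covariate point holds in conditional form. With arm left out, the lesion contrast carries about 0.35 of any direct arm effect, or 0.05 to 0.59 over the corners of the stated confidence intervals. For assumed direct effects of 0.1 to 0.3 SD at the planned rates, the resulting 0.03 to 0.10 SD is small beside a minimum detectable difference of 0.65 SD. A reader should not infer a large or certain bias. The primary endpoint, the sample size and the randomised comparison of lesion rates are unaffected.

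**What to change.** Bring the abstract, Study objectives, End points, Neuropsychological assessment and Statistical analysis into line by naming two separate secondary endpoints.

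- **(a) Cognitive change by randomised arm**, with the covariates already stated.
- **(b) Cognitive change by new-lesion status**, labelled observational. Keep the stated covariates, including the test interval, and add randomised arm and pre-existing lesions on baseline MRI.

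Procedure duration or fluoroscopy time can be added to (b) as a sensitivity analysis. Both are to be recorded under Cardiac catheterization, and the Discussion reports that they are independently associated with infarction.

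The cost is wording and a few degrees of freedom in (b); no new data are needed. Adjustment will not make (b) a causal estimate, since lesion status is not randomised and residual confounding remains, so reports of (b) should say so.

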### Study population

Patients with severe aortic stenosis scheduled for cardiac catheterization because of aortic valve stenosis to assess coronary artery tree and aortic valve disease before surgery will be prospectively and consecutively invited to participate in the study. After informed consent is obtained the patient will be included. Exclusion criteria will be a contraindication to MRI or inability to give written informed consent.

### Cardiac catheterization

All patients will be examined clinically by a senior physician and assessed for any history of previous cerebral embolism. Transthoracic echocardiography, 12-lead surface electrocardiogram, and coronary angiography will be performed for all patients. Cardiac catheterizations will be undertaken by expert interventional cardiologists using a standard Seldinger technique using 5 French (F) catheters either by TRA or TFA according to randomization assignment. Sheaths will be removed immediately after the procedure in all patients. Unfractionated heparin (50 iu/kg) will be given intravenously to all patients at the beginning of the procedure. Retrograde catheterization of aortic valve will be attempted in a right oblique projection using a long exchange guidewire (0.035 inch, 260 cm length to ensure exchange of the pigtail catheter) using a left amplatz 1 catheter or a right Judkins catheter [15]. During attempts to cross the aortic valve, the wire will be regularly withdrawn and cleaned and the catheter flushed every 2 minutes according to Grossman's recommendations [16]. When the pigtail catheter is placed in the left ventricle, the wire will be withdrawn and the catheter vigorously aspirated and pressure measurements performed. After left ventriculography, the catheter will be rapidly withdrawn from the left ventricle into the ascending aorta with simultaneous pressure measurements. Maximum and mean pressure gradients will be established. The duration of the whole procedure and fluoroscopic time in all patients will also be recorded.

### Magnetic resonance imaging

MRI will be done within 24 hours before, and 48 hours after, cardiac catheterization. MRI will be performed with a 1.5 Tesla system. The imaging protocol will include a DW single-shot spin echo echoplanar sequence acquired in the Anterior Commissure-Posterior Commissure plane with 24 contiguous sections (diffusion gradient b values of 0 and 1000 s/mm^2^, repetition time TR 6000 ms, echo time TE 120 ms, slice thickness 6 mm with no gap, matrix of 128 × 128 pixels, and field of view of 240 mm); fluid attenuated inversion recovery (FLAIR; TR/TE 10000/160 ms, TI 2200 ms); and T2-weighted turbo spin echo sequences (TR/TE 3500/94 ms). For DW-MRI, the diffusion gradients will be successively and separately applied in three orthogonal directions for a total acquisition time of 24 seconds. Trace images will then be generated and apparent diffusion coefficient (ADC) maps calculated with a dedicated software tool available on all recent MRI machines. The image analysis will be performed independently by two experienced neuroradiologists who will be blinded to the clinical data and will be unaware of the technical aspects of the angiographic cardiac procedure. For analysis of DW-MRI, the neuroradiologists will be asked to determine the presence, size, number, and vascular distribution of any focal diffusion abnormalities (bright lesions) in a pattern consistent with embolic lesions. Typical positive DW-MRI showing bright lesions (cerebral infarct) in asymptomatic patients are shown in Figures 1 and 2.

**Figure 1 F1:**
[figure not shown]
Typical positive DW-MRI (diffusion weighted-MRI) in asymptomatic patient confirming a recent cerebral infarction before catheterization.

**Figure 2 F2:**
[figure not shown]
Typical positive DW-MRI (diffusion weighted-MRI) in asymptomatic patient confirming a new lesion appeared after cardiac catheterization.

### Transcranial Doppler

Transcranial Doppler studies for this work will be performed in a subgroup of patients with the TCD power M-mode Doppler (PMD) 100 (Spencer Technologies, Seattle, WA), which calculates a PMD image concurrently with a single-gate spectrogram as previously described with a threshold of 2 MHz [17]. Bilateral power M-mode TCD will be recorded during cardiac catheterization through the temporal bones of patients with an automatic detection of microemboli. The PMD image shows depth from the probe on the vertical axis, time on the horizontal axis, and power of the Doppler shift signal at specific depths as color intensity. Simultaneously, the direction of blood flow is derived from the positive or negative mean value of the Doppler shift signal at the particular depth. This mean velocity information is used in the PMD image as red, depicting flow toward the probe, and blue as flow away from the probe.

Microembolic signals present a unique signature or "track" in the PMD image, which defines them as representing emboli. These potential embolic tracks in the middle cerebral arteries (MCA, red) and the anterior cerebral arteries (ACA, blue) PMD images have simultaneous spectrogram signatures. However, the spectrogram signatures are restricted to the point in time that the PMD embolic track crosses the gate depth associated with the spectrogram (yellow line). The potential MCA microembolus, which moves toward the probe as time progresses, will have a positively sloped track within the image consistent with its movement direction. The ACA microembolus, which moves away from the probe as time progresses, will have a negatively sloped track within the image. High-power/high-intensity, transient unidirectional signals correspond to the definition of microembolic signature approved by the Consensus Committee of the 9^th ^Cerebrovascular Hemodynamics Symposium [18]. Typical recordings of microembolic signals during cardiac catheterization are shown in Figure 3 and 4.

**Figure 3 F3:**
[figure not shown]
Typical microembolism signals (MES) recorded during cardiac catheterization. Isolated MES during catheter manipulation. By convention in our center upper part is for right carotid system and lower part for the left side.

**Figure 4 F4:**
[figure not shown]
Typical microembolism signals (MES) recorded during cardiac catheterization. Shower of MES during left ventriculography. By convention in our center upper part is for right carotid system and lower part for the left side.

### Neuropsychological assessment

Patients will undergo neuropsychological assessment within 24 hours before, and 48 hours after, cardiac catheterization. All patients with documented cerebral infarction at DW-MRI will be asked to come back for a new neuropsychological assessment at 1 year follow-up.

The aim of the cognitive testing is to provide clinical evidence of potential cerebral damage after cardiac catheterization and to quantify this potential cognitive decline allowing comparison of two groups of patients explored either by radial or femoral approaches. The tests must be sensitive enough to detect potential post-procedure cognitive decline and also able to explore different brain areas. Most of the neuropsychological tests that will be administered have been reported to be sensitive to change after CABG or PCI procedures [19] and will include: Digit Span Forwards and Backwards, Trail making test A and B, Wechsler Memory Scale visual reproduction test, Rey-Osterrieth's figure test, Grober-Buschckle's test, Rey Auditory Verbal Learning Test, Verbal fluency test, and Confrontation naming test.

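### The early radial-versus-femoral cognitive comparison is not protected from a possible hand effect of the wrist puncture

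*Protocol article*

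**What the plan says.** The abstract of the protocol article (Study design) states: "Secondary end-points include comparison of neuropsychological test performance and number of microembolism signals observed in the two groups". It adds that the tests are recorded in a subgroup, whose size is not given. The Neuropsychological assessment section repeats the aim, to "quantify this potential cognitive decline allowing comparison of two groups of patients explored either by radial or femoral approaches", and sets the timing: "Patients will undergo neuropsychological assessment within 24 hours before, and 48 hours after, cardiac catheterization". The only later test is selective: "All patients with documented cerebral infarction at DW-MRI will be asked to come back for a new neuropsychological assessment at 1 year follow-up".

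The battery includes "Trail making test A and B, Wechsler Memory Scale visual reproduction test, Rey-Osterrieth's figure test". The other listed tests are Digit Span, Grober-Buschke, Rey Auditory Verbal Learning, verbal fluency and naming.

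Under Statistical analysis, "The compound score for global cognitive function will be constructed by calculating the average of the z scores for all the above tests". Decline is baseline z minus follow-up z, for memory, psychomotor speed and global function. Adjustment is for age, sex, education and the interval between tests. Which tests form each domain is not stated.

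Under Cardiac catheterization, radial or femoral access follows the randomization and the radial side is not fixed. The Background rationale favours one side: "right TRA, which avoids crossing the aortic arch could reduce the risk of mobilization of atherosclerotic plaque". It also says that radial access has fewer local complications.

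**The concern.** The baseline test comes before the puncture and the retest follows within two days. If the writing hand is sore, dressed or guarded at the retest, that enters the change score of every pen test, and it can do so only in the radial arm. The assigned access would itself be the cause, so randomization does not balance the effect. Masking the examiner does not remove it, and none of the four covariates captures it. The composite then mixes hand function with cognition.

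At stake is the reading of the arm comparison. A hand effect could look like more brain injury with radial access, or could hide a cognitive benefit of radial access, which is the direction in which the trial expects fewer lesions. Because only patients with infarction are retested at 1 year, no later comparison of the whole arms could correct the early one.

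**Working it through.** **The plan's own figure.** The article gives no sample size or effect size for the cognitive comparison. Its 152 patients (76 per arm) are for the DW-MRI primary end-point. With 23% versus 5.9%, two-sided 5% and 80% power, the continuity-corrected formula gives 77 per arm (154 in total), so that figure reproduces closely. It does not depend on this point; 76 per arm is used below only as the largest number that could be tested.

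**Share of hand-done scores.** Digit Span and Trail Making count as two scores each. Hand-done: Trail Making A, Trail Making B, visual reproduction, Rey-Osterrieth figure = 4 of 10. Spoken: 6 of 10. If paired parts are merged, the hand-done share is 3 of 8 = 0.375.

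**Size of the shift.** Let f be the share of radial patients whose writing hand is still impaired at the retest, and h their loss in SD units on hand-done tests, with all scores aligned so that higher is better.
- Global score: shift = 0.4 × f × h (0.375 × f × h if pairs are merged).
- Psychomotor speed, if it consists of Trail Making alone: shift = f × h.

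**Assumptions not in the documents.** Change-score SD of 1 per test; correlation of changes 0.5 between Trail Making A and B, and 0.3 across the battery; h = 0.5; no true cognitive difference; two-sided 5% z test. The small extra spread from only some patients being affected is ignored.
- SD of a mean of k scores = √[(1 + (k − 1)ρ)/k]. Speed: √(1.5/2) = 0.866. Global: √(3.7/10) = 0.608.
- SE = SD × √(2/n). At n = 76 per arm: 0.1405 (speed) and 0.0987 (global).
- False-positive rate = Φ(shift/SE − 1.96) + Φ(−shift/SE − 1.96).

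Example, f = 50%, n = 76. Speed: 0.25/0.1405 = 1.78, giving 42.8%. Global: 0.10/0.0987 = 1.01, giving 17.3%.

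| f (h = 0.5) | Shift, speed / global | 76 per arm, speed / global | 38 per arm, speed / global |
|---|---|---|---|
| 5% | 0.025 / 0.01 | 5.4% / 5.1% | 5.2% / 5.1% |
| 10% | 0.05 / 0.02 | 6.5% / 5.5% | 5.7% / 5.2% |
| 25% | 0.125 / 0.05 | 14.4% / 8.0% | 9.6% / 6.5% |
| 50% | 0.25 / 0.10 | 42.8% / 17.3% | 24.2% / 11.1% |
| 100% | 0.50 / 0.20 | 94.5% / 52.7% | 71.1% / 30.0% |

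The 38-per-arm columns show a tested subgroup of half the sample, also an assumption. With 3 of 8 tests, the global rate at f = 50% and 76 per arm is 15.3% instead of 17.3%.

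**Against the signal sought.** The planned lesion difference is 23% − 5.9% = 17.1 points. If a new lesion cost 0.5 SD on every test (assumption), the true arm difference would be 0.171 × 0.5 = 0.086 SD. A hand loss of 0.5 SD would cancel it at f = 0.086/0.5 ≈ 17% for speed, and at f = 0.086/0.2 ≈ 43% for the global score.

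**Direction.** Trail Making is scored as time, and the article does not say that its z score is reversed. Unreversed, a slower hand would count as improvement: speed would shift by the same size in the other direction, and with equal shifts the four hand-done scores would offset each other in the global score (2/10 − 2/10 = 0).

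**The case against.** A reader might infer that hand impairment in the radial arm is in fact scored as cognitive decline. The documents do not support that. They report no soreness, dressing or loss of hand function after radial access and give no rate. The effect needs the writing hand to be the punctured one and still impaired at the retest. The side is not fixed; the mention of the right side is rationale, and that the right hand is usually the writing hand is an assumption. That it would count as decline also assumes that Trail Making times are reversed.

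The battery is not mainly manual either: six of ten scores are spoken. False-positive rates of 50% or more, which a reader could produce, need a large average loss across the whole radial arm, for which nothing in the article speaks. The comparison is secondary, concerns a subgroup, and appears in the abstract and in the aim of the testing, whereas the End points section names the effect of silent infarction on cognition. Puncture side, test conditions and domain scoring may be in the full protocol. All of this stands, and it limits the point to a possible bias of unknown size.

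The statement that radial access has fewer local complications only partly answers the point. Femoral discomfort could lower scores too, so the net direction over the whole battery is uncertain. But a groin problem would not act selectively on pen tests, and a sore or dressed wrist need not be a complication.

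A comparison on spoken tests alone would also give up visuospatial function and psychomotor speed, against the stated aim of exploring different brain areas. That is a good reason not to replace the full score.

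**Conclusion.** The point holds as a gap in protection. The article fixes the battery, the 48-hour retest, the averaging and the covariates, and that combination cannot tell a hand effect from a cognitive one in the arm comparison. The bias ranges from negligible to large. With a 0.5 SD loss in 10% of radial patients the false-positive rate is 5.5% (global) to 6.5% (speed). With the same loss in half of them it is about 17% and 43% at 76 per arm, and about 11% and 24% at 38 per arm. These figures rest on assumed SDs, correlations and h, and the speed figures also on that domain being Trail Making alone. Memory tests answered by speech are not touched by this mechanism, and neither is the DW-MRI primary end-point. This is a cheap improvement to a secondary comparison, not a flaw in the main result.

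**What to change.** In Statistical analysis, keep the full battery and the global score, and prespecify beside them the same radial-versus-femoral comparison:
- on the mean of the spoken tests (Digit Span, Grober-Buschke, Rey Auditory Verbal Learning, verbal fluency, naming);
- separately on the hand-done tests, adding Trail Making B minus A, which largely removes motor slowing common to both parts.

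Record the puncture side and the writing hand, and show the hand-done tests by whether the writing hand was punctured. State in advance that an arm difference confined to hand-done tests cannot by itself be attributed to brain injury. State also which tests form psychomotor speed and that timed scores are reversed.

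The cost is two form items and some extra secondary analyses, with no additional tests, visits or patients. The spoken-only score is slightly less precise: under the same assumptions its SD is √(2.5/6) = 0.645 against 0.608, about 6% wider (0.645/0.608 = 1.06).
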